**Primary Study Endpoints**

| **Measure** | **Timing** |
| --- | --- |
| Five-Times Sit-to-Stand (FTSTS) test | Baseline, week 6 and week 12 |
| One-Legged Stance Test (OLST) | Baseline, week 6 and week 12 |
| 30 second chair test | Baseline, week 6 and week 12 |
| Exercise daily performance | Daily for 12 weeks |

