**Measures**

**Primary Outcome Measures**

**Functional Performance Measures**

The participants in both groups will complete three functional performance measures while being observed by a trained researcher over Zoom at baseline, week 6 and week 12 (The Five-Times Sit-to-Stand (FTSTS) test, part of the Short Performance Physical Battery(SPPB)), the One-Legged Stance Test (OLST) and the 30 second chair stand test. As with the coaching sessions, the participants will orient their camera so that the entire body will be visible to the researcher

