## Sample size determination

Effect size calculations are based on evidence that 30 second chair stand performance declines with age and predicts future functional decline. We considered a large effect size as healthier patients in our pilot showed large gains (i.e., *d > 1.00)* in squat performance, but because our intended sample has at least some degree of limitations with walking, we expect a more conservative effect of the intervention on measures of physical function (i.e., d = .60).

Based on a 2-group design (intervention, control) assuming a moderate standardized between-group difference at 12 weeks (Cohen’s d = .60), a sample size of 88 (44 per group) would be needed to detect a difference between groups with a two-sided significance level of 0.05 and 80% power. To account for an anticipated 20% attrition rate over the study period, we will recruit up to 110 participants.

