## Statistical analysis

Summary statistics (e.g., mean and standard deviation (SD) for continuous variables; frequency and proportion for categorical variables) will be reported for participant baseline characteristics. Baseline differences between randomly assigned participants will be evaluated with two-sample t-tests and Fisher’s exact tests. Changes in the primary outcome measures over 12 weeks will be evaluated at the group level using linear mixed-effect models to analyze change over time and the Group x Time interaction. The analysis will employ an intention-to-treat approach, with missing data addressed through mixed-effects modeling in the longitudinal data analysis framework. A two-sided *p*-value of less than or equal to .05 will be considered statistically significant.

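### Three between-group primary endpoints share an unadjusted 0.05 threshold with no rule for what counts as success, while the sample size is set for a single test at 0.05

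*Protocol*

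**What the plan says.** Protocol, Primary Study Endpoints: a table lists FTSTS, OLST, the 30-second chair test and daily exercise performance, with no order of importance. The three functional tests have the same schedule, for example "30 second chair test | Baseline, week 6 and week 12". Daily performance is recorded every day for 12 weeks.

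Protocol, Functional Performance Measures (under Primary Outcome Measures): "The participants in both groups will complete three functional performance measures while being observed by a trained researcher over Zoom". These are FTSTS, OLST and the 30-second chair stand. Daily exercise performance has no such statement. It comes from the daily exercise survey, and the Delayed intervention control section keeps controls on usual care until the 12-week follow-up is complete.

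Protocol, Sample size determination: the rationale begins "Effect size calculations are based on evidence that 30 second chair stand performance declines with age and predicts future functional decline". The effect is then stated more broadly: "we expect a more conservative effect of the intervention on measures of physical function (i.e., d = .60". On that basis "a sample size of 88 (44 per group) would be needed to detect a difference between groups" at a "two-sided significance level of 0.05 and 80% power". Allowing for 20% attrition, up to 110 are recruited.

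Protocol, Statistical analysis: change in the primary outcome measures (plural) is analysed by linear mixed-effects models with a Group x Time interaction. One threshold is given: a two-sided p-value "of less than or equal to .05 will be considered statistically significant".

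**The concern.** The sample size section spends the 5% error rate once, on one comparison. The endpoint and analysis sections make it available to several primary measures. Nothing in the protocol says which result decides the trial: there is no single primary, no testing order, no split of alpha and no requirement that all succeed. The Study Hypothesis does not settle it, because it refers to measures of lower extremity performance without saying how many must improve.

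The gap matters most if results are mixed. If one of three functional tests reaches p ≤ 0.05 and two do not, the protocol gives no basis for calling the trial positive or negative, and a choice made after seeing the data cannot restore error control. A positive claim resting on whichever test succeeded would carry more than the nominal 5% false-positive risk.

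**Working it through.** **Inputs from the protocol.** d = 0.60, two-sided alpha 0.05, 80% power, 44 per group, 20% attrition (Sample size determination). Three primary measures are taken in both groups (Functional Performance Measures). The threshold is p ≤ 0.05 (Statistical analysis). The protocol gives no correlations between the tests, so those below are assumptions.

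**1. The plan's own figure.** Per group, n = 2(1.960 + 0.842)² / 0.60² = 43.6, rounded up to 44, so 88 in total. Recruitment is 88 / (1 − 0.20) = 110. Both match the protocol. A t-based calculation gives 44.6, so 45 per group; at 44 per group the power is 80.4% (normal) or 79.5% (t). The stated size is right for one test.

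**2. How many between-group tests.** Four measures are listed. Controls do not perform the exercise programme during the 12 weeks, so a Group x Time test of daily performance does not look feasible. The count used here is three.

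**3. Chance of at least one false-positive result among three tests at 0.05, with no true effect.**

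| Assumption | Chance |
| --- | --- |
| Upper bound, 3 × 0.05 | 15% |
| Independent, 1 − 0.95³ | 14.3% |
| Correlation 0.5 between the chair tests, 0.2 with OLST | about 13.4% |
| Correlation 0.7 between the chair tests, 0.3 with OLST | about 12.6% |
| Correlation 0.9 between the chair tests, 0.5 with OLST | about 10.8% |

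The correlated rows come from 2 million simulated draws of three normal test statistics, counting draws with any |z| > 1.96. Even with all three correlated at 0.9, the figure is 8.3%. Every scenario examined exceeds 5%. Week 6 tests are not counted.

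**4. What the possible repairs do to power, at 44 per group.**

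- *One named primary at 0.05:* 80.4% (normal) or 79.5% (t), unchanged.
- *Bonferroni at 0.05/3 = 0.0167:* power for one given endpoint is 66.3% (normal) or 64.6% (t). If d = 0.60 holds for all three measures, power for at least one success is about 89% to 91% at correlations of 0.5–0.7 and 0.2–0.3 (simulation, normal approximation).
- *Bonferroni with 80% power kept for each endpoint:* 59 to 60 per group, so 118 to 120 evaluable and 148 to 150 recruited.

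**The case against.** **The statistical analysis plan may settle it.** Testing order and alpha allocation are often left to that plan, and it is not shown. This stands as a condition on the size of the problem. It does not remove the point, because which endpoint is primary is a protocol matter, and this protocol has already named four and fixed the threshold.

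**No rule says that any one success is enough.** A reader might infer that the protocol declares the trial positive on any single significant primary. It does not: the threshold is general, and a requirement that all primaries succeed is not ruled out. Under that requirement there would be no inflation. But it is not stated either. The fair charge is a missing decision rule, and 11% to 14% is the consequence of one reading that the text allows.

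**Four tests, or more with week 6.** A reader might count four between-group tests, for 18.5% if independent. The text supports three. Nor does it say that week 6 is tested separately; the hypothesis, the sample size and the analysis all refer to 12 weeks.

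**The power statement.** A reader might conclude that the 80% power belongs to the chair stand alone. The chair stand is the only outcome test named in the rationale, but d = 0.60 is stated for measures of physical function in general. The 80% therefore applies to any one measure with that effect.

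**Bonferroni is not shown to be too costly.** The drop to 64.6% is for one given endpoint, whereas power for at least one success would be about 89% to 91%. Preferring a single primary is a choice among valid options. It rests on simplicity and on keeping the sample size calculation as it stands.

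**Conclusion.** The concern holds in a limited form. The protocol has three between-group primary endpoints, one unadjusted 0.05 threshold, no statement of what constitutes success, and a sample size that budgets alpha for one comparison. If success were claimed on any one of the three, the false-positive chance would be 14.3% under independence and about 11% to 13% under the assumed correlations (0.5 to 0.9 between the chair tests, 0.2 to 0.5 with OLST). The exact figure rests on those correlations; the direction does not.

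It does not follow that 88 or 110 is wrong, since both reproduce for a single test. Nor do the documents establish that the trial will run at 14%: that depends on a decision rule that the protocol omits and that a statistical analysis plan could supply. The rule needs to be fixed before any between-group results are seen.

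**What to change.** Amend Primary Study Endpoints, Primary Outcome Measures and Statistical analysis together:

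- Name the between-group difference in 30-second chair stand count at week 12 as the single primary endpoint, tested at two-sided 0.05. It is the only outcome measure that the sample size rationale names.
- Make FTSTS and OLST at week 12 key secondary endpoints, tested only if the primary succeeds. Use Holm across the two: the smaller p-value against 0.025 and, if that passes, the larger against 0.05.
- Reclassify daily exercise performance as a descriptive secondary outcome within the intervention group.
- State that week 6 results are supportive.
- Carry the same wording into the statistical analysis plan.

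Cost: FTSTS, OLST and daily exercise performance lose the label of primary, and a benefit seen on FTSTS or OLST alone could not be claimed as confirmatory. The 88 evaluable and 110 recruited, the visits and the alpha of 0.05 do not change.

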### Criteria for removal from study

Participants may be from the study if they become injured and cannot exercise or if they are asked by their Primary Care Provider to suspend exercise. The Principal Investigator reserves the right to remove a participant from the study for any reason, based on their discretion, particularly a belief that continued participation exposes them to unnecessary risk. Also, participants have the right to withdraw themselves at any time and halt all study-related activities permanently.

Other withdrawal criteria include: unwillingness to follow protocol during visits, unwillingness to complete study visits, and/or return of equipment to study staff, withdrawal of consent by the participant, development of a new medical problem that would exclude them from the study.
